#### Behavior change techniques

The behavior change techniques incorporated into the app align with the underlying theoretical model (Fig. 1) and can be subdivided in techniques targeting motivation (stage 1), volition (stage 2) and habit formation (stage 3). Table 1 gives an overview of the behavior change techniques covered by the app, the stages of behavior change, the mechanisms of action through which individual behavior change techniques have their effects [60] and how techniques are implemented in the app. All techniques are labelled according to the taxonomy of behavior change techniques (compiled by Michie and colleagues, [61]).

**Table 1 Tab1:** Overview of behavior change techniques, mechanisms of action and implementation modes

Behavior Change Technique	Mechanism of action	Implementation mode
**Stage 1 – motivational**		
Goal setting (1.1) Goal setting outcome (1.3)	Behavioral regulation (intention) Goals	During the initial wizard, intended to tailor the app’s content at best possible to participants’ needs, work and private situation, participants are asked to set an individual health goal. An interactive goal setting worksheet is available to support participants in setting goals correctly. Note, participants are not specifically guided to differentiate between behavioral (e.g., set the goal of eating 5 pieces of fruit per day) and outcome goals (i.e., set a weight loss goals of 0.5 kg per week) but to choose a personally relevant health goal
Instruction on how to perform the behavior (4.1) Demonstration of the behavior (6.1)	Knowledge (self-efficacy) Beliefs about capability skills Social learning/imitating	The within-app exercise and task catalogue offers videos, written information and instructions on how to perform physical activity, and mindfulness behaviors. The videos feature a nurse executing the behavior correctly. By observing and imitating the nurse, self-efficacy is enhanced and beliefs are built that participants are able to achieve what the role model (i.e. nurse) achieved, raising expectations of success and motivating participants to work hard towards their goals
Information about health (5.1) and emotional (5.6) consequences	Knowledge Beliefs about consequences (positive, negative outcome expectancies) Attitude towards the behavior Perceived susceptibility/ vulnerability Intention Emotion	Blog articles (“highlights of the day”), covering different health topics related to physical activity, nutrition and mindfulness behaviors, are presented on the home screen and offering information about positive and negative health consequences, affecting participants’ knowledge, outcome expectancies, attitudes, perceived personal risk, emotional state and in turn their intentions. Additionally, “knowledge elements” of exercise and task suggestions included in within-app exercise catalogue offer information about health consequences that are supposed to have similar effects on aforementioned social-cognitive variables
**Stage 2—volitional**		
Action planning (1.4)	Behavioral regulation (action initiation)	Based on the goal setting instructions upon the initial wizard, participants are prompted via a newsletter sent to participants approximately 3 weeks post-baseline (booking date + 25), to make a plan by specifying how they want to achieve their intended behavior, what they want to do, where they want to do it and when. Action planning helps people to act in favorable situations and by anticipating contexts suitable for behavioral execution, which facilitates developing cue-behavior associations. Action planning as such can make cues more easily accessible in memory so that when exposed to the cue, it is more likely that the behavior is executed
Self-monitoring of behavior (2.3) Feedback on behavior (2.2) Discrepancy between current behavior and goal (1.6) Remove access to reward (7.4)	Behavioral regulation (action control) Knowledge	The home screen of the app features three progress bars (i.e., for physical activity, nutrition, mindfulness). Upon exercise/tasks completion a box can be ticked off. Ticking boxes (i.e., indicating completion of exercise/task) directly transfer to the progress bars, reflecting progress for the given behavior. Additionally, in case participants focus too much on one behavior and ignore another, negative progress is indicated in progress bars for the neglected behavior. Through this feedback and these gaming elements, participants can easily monitor their behaviors and goal progresses (positive, negative)
**Stage 3 – habit formation**		
Prompts/cues (7.1) Behavioral practice/rehearsal (8.1) Habit formation (8.3)	Memory, attention, decision processes Behavioral cueing Beliefs about capabilities Behavioral regulation	Via a newsletter participants receive an interactive worksheet stressing the importance of determining specific contextual cues (e.g., reoccurring situation or context such as lunch breaks) in which they intend to execute the behavior (e.g., stretching neck). Selecting triggers facilitates developing cue-behavior associations, which fosters the habit formation process. Additionally, the feature “open tasks” on the home screen continuously remembers participants to practice their favorite exercises and tasks
**Stage independent**		
Social support (unspecified) (3.1)	Social influences Social/professional role and identity	Participants have the possibility to contact a trained coach (via email or phone) in case of questions, concerns, problems. The coach could also function as a role model, providing information and knowledge on health-related topics or providing support for habit formation (e.g., provision of feedback)

*Note.* Numbers in parentheses for each behavioral change technique are per BCTTv1. *BCTTv1* BCT Taxonomy version 1 ([62])

### Evaluation design

A one-arm, multicenter mHealth interventional study will be performed. Participants complete all assessments in the app with the same assessment rhythm irrespective of when participants enroll in the study. Upon registration, participants can complete questions on socio-demographic variables, psycho-social determinants (e.g., intention, self-efficacy), physical activity, nutrition and mindfulness as well as health-related outcomes (e.g., back pain). Data will be collected across a 100-day period at four assessment points: baseline (booking date + 0), interim after 4 weeks (booking date + 28) and 8 weeks (booking date + 56) and post-intervention (booking date + 99). Additionally, 11 weekly assessments will be scheduled (booking date + 7, + 14, + 21, + 35, + 42, + 49, + 63, + 70, + 77, + 84, + 91). Participants will receive reminder emails for the baseline and post assessment four days after the respective assessment date (i.e., baseline reminder booking date + 4 days, post assessment booking date + 104 days). Reminders for the remaining assessments are incorporated into the app (via “open tasks”, see Description of the intervention for further information). Outcome data will be the same for all participants, whether they continue or discontinue/deviate from the intervention protocol. One week after the completion of the intervention, a structured interview is scheduled with volunteers to gain insights in participants’ experiences with the app (e.g., practicability, operability, acceptability). Due to economic reasons, the total set of items varies per assessment point. The Fig. 3 presents an overview of the enrolment schedule, the intervention, worksheets and assessments.

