#### Psychosocial determinants of behavior change and habit formation

The following psychosocial determinants are assessed for physical activity, nutrition, and mindfulness behavior. Participants indicate their responses on a six-point Likert scale ranging from 1 (not at all true), 2 (not true), 3 (rather untrue), 4 (rather true), 5 (true) to 6 (absolutely true), if not otherwise specified. The baseline (t0), and post (t14) assessments focus on motivational (i.e., intention, outcome expectancies, self-efficacy) and volitional constructs (i.e., action planning), as well as on habit strength for physical activity, nutrition and mindfulness behaviors. The weekly assessments (t1, t2, t3, t4, t5, t6, t7, t8, t9, t10, t11, t12, t13) put focus on the habit formation process (i.e., self-monitoring, emotional states, context stability, intention, outcome expectancies) for all behavioral domains. Mean values and standard deviations are calculated to build the scales for the psychosocial determinants.

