##### Automaticity

Automaticity is assessed with four items by means of the subscale Self-Report Behavioral Automaticity Index from the Self Report Habit Index (SRHI) [65, 66] at baseline and post assessments, and with two items at interim assessments (due to economic reasons). Following the stem “Physical activity/ Eating five portions fruit and vegetables/ Practicing mindfulness activities three times per week for ten minutes … is something” participants indicate on a five-point Likert scale ranging from 1 (do not agree) to 5 (totally agree) if they engage in the behaviors for example “automatically”. The SRHI has proven to be a reliable and valid instrument to measure habit strength for physical activity (α = 0.96) [66].

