### Statistical analysis

Statistical analysis will be performed using SPSS Version 27 and conducted after completion of the data collection process. Interim analyses will not be performed. All primary outcome data will be screened for normal distribution by using the Shapiro–Wilk test. Data will be checked for outliers and missing data. Descriptive statistics will be run to explore the sample characteristics. Continuous variables will be presented as means and standard deviations, while categorical variables will be displayed by percentages of participants in each possible category. Intention-to-treat analyses will be conducted, given that drop-out rates are usually high in eHealth research [80], per protocol analysis are not feasible. Only data sets from participants who completed the baseline, post and 50% of the weekly assessments will be included in the analysis. To investigate difference between the sample of analysis and those who provided baseline data only, differences between baseline scores and a dichotomous attrition variable (i.e., 0 = not retained for analysis, 1 = retained) will be analyzed using χ^*2*^ and *t*-tests, followed by logistic regressions. To test for changes in habit strength, motivational (intention, self-efficacy, and outcome expectations), volitional constructs (action planning), health behaviors and health status from baseline to post assessments, analysis of variance with repeated measures and *t*-tests between subsequent measures will be run (hypothesis 1 a-e). To examine hypotheses 2–4, hierarchical multiple linear regression analyses will be conducted, with motivational, volitional and habit-related predictors at baseline to predict habit strength, health status and health behavior at post-assessment. To account for the hierarchically structure of data (i.e., repeated measurements nested within individuals) we plan to run two-level models with 13 assessment periods nested in participants (hypotheses 5 a-b, linear mixed models, LMM, [81]). LMM allows to test for simultaneous assessment of the effects of within-person variation in weekly assessments of behavior,habit strength and predictor variables (level 1) and between-person variables such as age, health status and other covaraites measured only once (level 2). Prior to running analyzes, the time parameters will be grand mean centered to minimize multicollinearity. Subsequently, various steps will be undertaken to determine appropriate model fit, as suggested by Field [81]. Once the model shows appropriate fit parameters, LMM can be conducted by selecting the Restricted Maximum Likelihood for estimation method [81]. In a model including all behavior-related cognitions and covariates simultaneously, motivational and volitional variables will be modeled at the between-person level (e.g., comparing persons with higher average versus lower average intentions) and the within-person level (e.g., assessments when intentions to engage in health behavior were higher-than-usual vs. lower-than-usual). Models will be run separately for each behavioral domain.

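### Every hypothesis is restricted to participants with half of the weekly forms, although hypotheses 1 to 4 need only baseline and post values, and the number of weekly forms is given as both 11 and 13

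*Protocol article*

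**What the plan says.** The inclusion rule stands in Statistical analysis: "Only data sets from participants who completed the baseline, post and 50% of the weekly assessments will be included in the analysis". It names no hypothesis and gives no denominator. The same paragraph announces intention-to-treat analyses and calls a per-protocol analysis not feasible.

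The term on which the rule depends is used for two different sets of forms:

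- Evaluation design names the main assessment points as baseline, "interim after 4 weeks (booking date + 28) and 8 weeks (booking date + 56) and post-intervention (booking date + 99"), and then says "Additionally, 11 weekly assessments will be scheduled", on the dates "booking date + 7, + 14, + 21, + 35, + 42, + 49, + 63, + 70, + 77, + 84, + 91". The +28 and +56 forms are not among them.
- The section on psychosocial determinants says "The weekly assessments (t1, t2, t3, t4, t5, t6, t7, t8, t9, t10, t11, t12, t13) put focus on the habit formation process". That is 13 forms.

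Statistical power and the mixed-model text in Statistical analysis also work with 13 measurement points or periods.

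The measurement sections describe the weekly content as "self-monitoring, emotional states, context stability, intention, outcome expectancies". The Automaticity section places the habit measure "at baseline and post assessments, and with two items at interim assessments (due to economic reasons"). Process evaluation identifies the interims as weeks four and eight.

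**The concern.** Under Objectives and Statistical analysis, hypothesis 1 concerns change from baseline to post, and hypotheses 2 to 4 predict post values from baseline values. None of them needs a weekly form. Requiring half of those forms removes people whose data for these hypotheses are complete, on the basis of how diligently they answered other questionnaires.

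Answering in-app forms is a sign of engagement with the app. The retained sample will therefore lean towards engaged users, and the pre-post changes will describe them rather than everyone who supplied both values. That sits badly with the intention-to-treat label.

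The uncertain denominator is a second, smaller problem: at the margin, two analysts following the text could admit different people.

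**Working it through.** **1. Count the forms.** The date list in Evaluation design has 11 entries, so the stated 11 reproduces. Adding +28 and +56 gives every seventh day from 7 to 91, which is 13 forms and matches t1 to t13, with the interims at t4 and t8. With baseline (t0) and post (t14) the total is 15.

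**2. Thresholds.** 0.5 × 11 = 5.5, so at least 6 forms. 0.5 × 13 = 6.5, so at least 7 forms.

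**3. What each hypothesis needs.**

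| Hypothesis | Values used | Weekly forms needed? |
|---|---|---|
| 1 a-e | baseline and post | no |
| 2 to 4 | baseline predictors, post outcome | no |
| 5 a-b | repeated measures over 13 periods | yes |

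**4. Where the two counts disagree.** Let w be the number completed of the 11 non-interim forms and k the number of the two interims. The rules are w ≥ 6 and w + k ≥ 7. They differ in two cells only:

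- w = 6, k = 0: in under 11, out under 13.
- w = 5, k = 2: out under 11, in under 13.

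Each cell holds C(11,6) = C(11,5) = 462 completion patterns, together 924 of 2^13 = 8192.

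**5. Participants with automaticity at +0, +28, +56 and +99.** Here k = 2. Under 11 they are excluded when w is 0 to 5. Under 13 they are excluded when w + 2 ≤ 6, so when w is 0 to 4. Exclusion is possible under both counts.

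**6. Illustrative size.** The documents give no completion rates. Assume that, among people with baseline and post, each of the 13 forms is completed independently with probability p. With X ~ Bin(11, p) and Y ~ Bin(13, p):

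- dropped: P(X ≤ 5) under 11, P(Y ≤ 6) under 13;
- dropped although both interims are done: P(X ≤ 5) under 11, P(X ≤ 4) under 13;
- classified differently: P(X = 6)(1 − p)² + P(X = 5)p².

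At p = 0.6 the last line is 462 × 0.6⁶ × 0.4⁵ × 0.4² + 462 × 0.6⁵ × 0.4⁶ × 0.6² = 0.035 + 0.053 = 0.088.

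| p | Dropped, 11 / 13 | Dropped despite both interims, 11 / 13 | Classified differently |
|---|---|---|---|
| 0.5 | 50.0% / 50.0% | 50.0% / 27.4% | 11.3% |
| 0.6 | 24.7% / 22.9% | 24.7% / 9.9% | 8.8% |
| 0.7 | 7.8% / 6.2% | 7.8% / 2.2% | 4.0% |
| 0.8 | 1.2% / 0.7% | 1.2% / 0.2% | 0.8% |

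**7. Missed forms in one final block.** If someone completes t1 to tk and nothing more until post, both rules fail for k ≤ 6 and both are met for k ≥ 7, because the first seven forms contain six non-interim forms and one interim. The disagreement is then zero.

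**The case against.** The 11 against 13 conflict can be read as one of labels. Evaluation design counts the dates added to the four main points, and the other section counts every form with weekly content. Since 11 + 2 = 13, and Statistical analysis itself uses 13 periods, 13 is the more natural denominator. This largely stands: the inconsistency is real, but it affects only two boundary cells, under assumed completion rates.

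A reader might infer that the conflict is what removes participants with every automaticity measurement. The documents do not support that. Step 5 shows that such people can be excluded under either count, so the cause is the form-count rule itself.

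A reader might also take it as settled that automaticity is absent from the ordinary weekly forms. The measurement sections say so, but Statistical analysis speaks of weekly assessments of habit strength, and the schedule figure (Fig. 3) is not shown. The remark about interim automaticity is therefore conditional on the measurement sections. The point about hypotheses 1 to 4 is not, because those hypotheses use baseline and post values wherever else automaticity is measured.

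It would also go too far to say that the denominator will be picked after the data are seen. A separate analysis plan may fix it.

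Finally, the protocol plans to compare retained and non-retained participants at baseline. That would describe the selection but would not restore the discarded pre-post data.

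**Conclusion.** The point holds in this form: one completeness rule governs all hypotheses, although four of the five hypothesis sets do not use the forms that it counts. It discards usable pre-post data and selects on engagement, contrary to the stated intention-to-treat aim. Under independent completion the loss among people with baseline and post is about 23% to 25% at p = 0.6, 6% to 8% at p = 0.7 and about 1% at p = 0.8. These rates are assumptions, and the real loss depends on how form completion clusters within people. That retained users are the more engaged ones is an inference from what the rule counts. The documents give no figure for its effect on the estimates.

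The denominator conflict is a minor addition: about 11% down to 1% classified differently for p from 0.5 to 0.8, and none with one final block of missed forms.

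**What to change.** In Statistical analysis, state that hypotheses 1 to 4 are analysed in everyone with the baseline and post values that the given analysis needs, with no requirement on weekly forms.

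If a form count is kept, apply it only to hypothesis 5 and define it once: at least 7 of the 13 forms t1 to t13, including +28 and +56. Align Evaluation design, the section on psychosocial determinants and Statistical analysis to that definition.

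The change needs no new data collection, but it is more than wording, since it alters who is analysed for hypotheses 1 to 4. The price is that the number analysed differs between hypotheses and must be reported for each. Settling the denominator does not settle whether habit strength is measured weekly. The measurement and analysis sections should be reconciled on that separately.

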### Study procedure

The current protocol focuses exclusively on the evaluation plan of a one-arm, multicenter mHealth interventional study and the post-hoc description of the Habit Coach app (i.e., after the development phase of the app). The trial is undertaken by independent external research experts in health and exercise psychology, presenting an important quality criterion for the project. Figure 2 depicts the study flow. Through the registration process in the app, written informed consent will be obtained from individuals. Upon registration, participants receive a 100-days access to the Habit Coach app. Besides the usual features, the app includes four interactive worksheets to aid the habit formation process, which have been specifically developed for this study by the team of independent experts in health and exercise psychology.

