### Weekly assessments with regard to favorite exercises and tasks

#### Self-monitoring

Self-monitoring of self-chosen favorite exercises is assessed with one single-item for physical activity, nutrition, mindfulness and app-user behaviors. Following the stem “In the last 7 days, on how many days did you practice your favorite exercises?”, participants indicate the frequency of behavioral engagement according to the following scale: 0 (not at all), 1 (once), 2 (twice), 3 (three times), 4 (four times), 5 (five times), 6 (six times) and 7 (daily).

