### Data management

All data are assessed through the mobile app, which will be extracted upon intervention completion in Excel files, before they are transferred in SPSS. All data collected during the various assessment waves will be stored in separate SPSS files, one file per assessment point. After data collection completion, data will be transformed in one SPSS file based on the participants’ identification numbers. Variable labels will be defined in SPSS. Additionally, information about the variables assessed is gathered in an excel codebook including variable names, labels, codes, specific item information etc. To prevent drop out, user will be contacted through reminder emails. Moreover, incomplete assessments and tasks will continuously be displayed on the home screen (i.e., “open tasks” feature). To ensure that instruments used are reliable and valid, only validated questionnaires will be utilized. To overcome data loss, all data will be stored on the servers of the Aeroscan company, which are hosted by the Domain Factory in Germany (domainfactory GmbH, [name]). The Domain Factory ensures reliability and unauthorized access to the servers. All data will be separately and confidentially stored at two different data bank systems and in line with the German data protection ordinance, ensuring a strict separation between the user’s identity (i.e., contact data) and psychosocial and demographic data. Only a few specifically trained Aeroscan IT experts can access the data. The few people with data access signed a confidentiality agreement. As long as the data are not effectively anonymized, no data usage will be conducted by the Aeroscan company, the company health care insurance or else. Only the research team (i.e., two professors, one post-doctoral researcher, one student assistant) has access to the data until anonymization. Upon termination of the study, all user data will be deleted.

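### The post form falls due at the end of the 100-day access and its reminder comes after it, and late forms keep their nominal assessment dates

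*Protocol article*

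**What the plan says.** On access, Study procedure in the protocol article states: "Upon registration, participants receive a 100-days access to the Habit Coach app". Evaluation design adds: "Participants complete all assessments in the app with the same assessment rhythm irrespective of when participants enroll in the study". The same section has data collected over a 100-day period and lists the last assessment as "post-intervention (booking date + 99)". Objectives and the semi-structured interview section instead place the post assessment 100 days after baseline.

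On reminders, Evaluation design says: "Participants will receive reminder emails for the baseline and post assessment four days after the respective assessment date". It then gives the dates as +4 for the baseline and "post assessment booking date + 104 days" for the post form.

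On overdue forms, Data management says that "incomplete assessments and tasks will continuously be displayed on the home screen", and the limitations paragraph repeats that incomplete questionnaires are kept available there. The weekly self-monitoring item asks: "In the last 7 days, on how many days did you practice your favorite exercises". The weekly intention item looks ahead over the same span.

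On use of the data, Data management stores one file per assessment point. Statistical analysis models 13 assessment periods nested in participants. It includes only those who completed the baseline, the post form and half of the weekly assessments.

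**The concern.** There are two timing problems, and both reach the analysis.

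The first concerns the post form. It is one of the forms that decide who is analysed, yet it falls due when access is about to end, and its e-mail reminder is dated after that. If access ends as stated, someone who misses the due date gets a reminder that cannot be acted on. That person is then lost not only to hypotheses 1 to 4, which use the post values, but also to hypothesis 5, whose weekly mixed model does not otherwise need a post form.

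The second concerns late forms. Keeping them available limits missing data, but the weekly items are anchored to the day of completion. A form answered weeks late describes the wrong week under its label, which blurs the time axis and the next-week lag of hypothesis 5. A baseline completed after app use has begun is no longer a pre-exposure value, although it is the reference for hypothesis 1 and supplies the predictors or covariates for hypotheses 2 to 4.

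**Working it through.** **Inputs** (offsets from the booking date): access 100 days (Study procedure); post form +99, post reminder +104, reminder rule of 4 days, weekly forms +7 to +91, interim forms +28 and +56 (all Evaluation design).

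**1. Reminder dates.** Reminder = due date + 4.
- Baseline: 0 + 4 = +4, as stated.
- Post: 99 + 4 = +103, not the stated +104.
- With the post form at +100, as Objectives words it: 100 + 4 = +104. That matches, but contradicts +99.

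**2. Position relative to the end of access.** The last access day is +99 if the booking day counts as day 1, and +100 if it does not.

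| Last access day | Days on which the post form can be completed | +104 falls after the end by | +103 falls after the end by |
|---|---|---|---|
| +99 | 99 − 99 + 1 = 1 | 104 − 99 = 5 days | 103 − 99 = 4 days |
| +100 | 100 − 99 + 1 = 2 | 104 − 100 = 4 days | 103 − 100 = 3 days |

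Correcting the one-day slip does not bring the reminder inside the period on either count.

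**3. What a missing post form draws on.** Statistical power gives 228 participants, allowing for 30% attrition. If 228 is the number recruited, the allowance is 0.30 × 228 = 68.4, or about 68 people. Everyone lost for want of a post form comes out of that allowance. The article gives no figure from which to predict how many that would be.

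**4. How late an overdue form can be.** With access to +99, the maximum delay is 99 minus the due date (one day more if access runs to +100):

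| Form | Maximum delay |
|---|---|
| Baseline, +0 | 99 days |
| +7 | 92 days |
| +21 | 78 days |
| +28 | 71 days |
| +56 | 43 days |
| +91 | 8 days |

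As an illustration, a +21 form filled in at +63 is 63 − 21 = 42 days late. Its seven-day recall covers +56 to +63 instead of +14 to +21, the same week that the +63 form covers. Several overdue forms completed in one sitting would share one recall period under different week labels, and each would count toward the 50% rule.

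**5. Baseline.** The favourites worksheet goes out at +0 and the wizard appears at first log-in. Informed consent is the only stated condition for access. A baseline prompted by the +4 reminder, or later by the open-task list, can therefore follow the first use of the app.

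**The case against.** The strongest reply is that lockout is nowhere stated. The article grants 100 days of access to the app but does not say what happens to a pending questionnaire afterwards. A reminder planned for +104 suggests that the authors expect the form to be reachable then. This stands. A reader might infer that anyone who misses +99 cannot complete the post form, but that is an inference from the access period and in-app completion. What remains is that the stated dates conflict and no extension is written down.

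A reader might also infer that overdue forms stay open indefinitely. The text says only that they are displayed continuously. If access ends, every in-app form ends with it, so the delay is bounded as computed above.

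It can also be said that form windows belong in the full protocol or the app specification, and that the schedule figure is not shown. That excuses the lack of detail on windows. It does not excuse the arithmetic conflict, nor the stated choice to keep overdue forms available alongside day-anchored items. How often forms would be completed late is unknown.

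On the baseline, the objection has force. Favourites are to be chosen over the first weeks, the goal-setting sheet is optional, cue selection and action planning arrive at +14 and +25, and some measures look back four weeks or a month. A few days' delay may matter little for those. A reader might infer that late baselines bias change toward zero. That would follow if early use raised scores, but nothing in the article establishes it for every outcome.

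**Conclusion.** The point holds in two parts. First, the access period, the post date and the reminder date do not fit together. The reminder is one day off the article's own rule, and on any count it falls 3 to 5 days after the stated access and data-collection period. The one- or two-day window for the post form assumes that access ends as stated and is not extended, which needs confirming.

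Second, late forms remain available for up to 92 days for the first weekly form and 99 for the baseline, while the files and the model are organised by nominal assessment. The possible size of the mislabelling is clear, but its frequency is not. The direction of any baseline bias is open.

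This should be corrected because the analysis set depends on the post form and the correction is cheap. It does not by itself invalidate the design.

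**What to change.** - **Dates.** Reconcile the access period, the post date (+99 or +100) and the reminder date. Keep the questionnaires, and only the questionnaires, reachable for a fixed, stated window after +99, and send the reminder inside it.
- **Weekly forms.** Record the completion date of every form. Assign each weekly form to the week it actually describes, or use completion time as the time variable in the mixed model for hypothesis 5. Do not count a form completed outside its week under its nominal label.
- **Baseline.** Flag baselines completed after the first logged exercise, and run a sensitivity analysis without them for hypotheses 1 to 4. This leaves delivery of the intervention unchanged; withholding the exercise catalogue until the baseline is submitted would alter it and is not needed.

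The cost is some app configuration, a stored timestamp and a few sentences. The drawback is that some weekly forms become missing or are reassigned. Under the present rule that could take a participant below the 50% threshold, and so out of the analysis before any mixed model is fitted. The two rules must therefore be set together. Simply locking weekly forms would have the same effect and should not be adopted on its own.
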